#### *6.7.7.1 Pre-screening*

---

Patients receiving care at the investigative sites will be pre-screened as potential subjects for the study. In order to do so, only the existing information obtained per standard routine medical procedures will be used. Pre-screening information (without identifiable information) will be obtained and transferred to Sponsor/ CRO. No study-specific screening procedures, activities or questionnaires will be performed during the pre-screening.

#### *6.7.7.2 Screening/Enrollment*

---

Patients considered potential candidates for the study based on pre-screening will sign an Institutional Review Board (IRB)/Review Ethical Board (REB)/Ethical Review Committee (ERC) approved ICD prior to participating in any study activities.

The following procedures are performed during the visit:

- Obtain signed ICD, place it in the patient file, provide copy to subject
- Obtain signature on the health information release form (when applicable)
- Assign a Subject Investigational Code (SIC)
- Verify that the patient meets all inclusion/exclusion criteria and perform the following:
  - Demographics
  - Screening clinical laboratory blood tests (liver enzymes (ALT/SGPT and AST/SGOT), creatinine, ANC)
  - Pregnancy test (if applicable)
- Perform and record ISNCSCI examination
- Review and verify all data collected to confirm the subject meets all study inclusion/exclusion criteria
- Check Screening Source Worksheets (SW) for completeness
- **Enroll subject:** Perform randomization procedure and enter randomization code into the Randomization Log
- Ensure Screening Form is updated with the enrollment information
- Administer *Dose # 1* of Investigational Drug and record on the Investigational Drug Dispensing SW
- Log the subject's medication accountability information into the Investigational Drug Accountability Log
- Log Investigational Drug administration into Medication Compliance SW
- Make a note in the subject's chart not to take medications on the exclusion list for 14 days
- Complete Charlson Comorbidity Score
- Obtain Injury Severity Score
- Subject completes questionnaires (recall of the status prior to the injury)
  - SF-36v2™, EQ-5D
- Obtain socio-economic, health behavior, medical history and information about concomitant medications
- Complete Spine Trauma Injury Data SW
- Record date and time of hospital admission
- Check and record concomitant medications
- Obtain and record vital signs

- Ensure the subject receives Investigational Drug during the hospital stay
- Record date and time of injury and other injury details
- Check Enrollment SWs for completeness
- Verify data and enter into electronic Case Report Form (eCRF) preferably within 48 hours but no later than 14 calendar days from collection

#### *6.7.7.3 Surgery*

---

- Record operative data
- Check and record concomitant medications
- Obtain and record intra-operative complications
- Record immediate postoperative AE/SAE
- Obtain and record vital signs
- Check SWs for completeness
- Verify data and enter into eCRF preferably within 48 hours but no later than 14 calendar days from collection

#### *6.7.7.4 72 hours $\pm$ 12 hours*

---

The following activities should be performed during the visit:

- Perform and record ISNCSCI
- Obtain and record concomitant medications
- Obtain and record AE/SAE
- Obtain and record vital signs
- Order clinical lab tests
- Obtain MRI between 48 -72 hours post-injury (at the discretion of the investigator or if standard of care)
- Check SWs for completeness
- Verify data and enter into eCRF preferably within 48 hours but no later than 14 calendar days from collection

#### *6.7.7.5 7 days $\pm$ 1 day*

---

The following activities should be performed during the visit:

- Order clinical lab tests
- Obtain and record concomitant medications
- Obtain and record AE/SAE
- Check SWs for completeness
- Verify data and enter into eCRF preferably within 48 hours but no later than 14 calendar days from collection

#### *6.7.7.6 14 days $\pm$ 2 days*

---

The following activities should be performed during the visit:

- Obtain and record concomitant medications
- Obtain and record AE/SAE
- Obtain and record vital signs
- Investigator performs and records:
  - ISNCSCI
  - SCIM
  - GRASSP evaluation (if discharge from acute care has not yet happened)
- Order clinical lab tests
- Subject completes questionnaires for:
  - Pain NRS
- Complete Medication Compliance SW
- Schedule next study visit
- Check SWs for completeness
- Verify data and enter into eCRF preferably within 48 hours but no later than 14 calendar days from collection

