#### 6.3.3 Other Endpoints

---

- Change in ISNCSCI Sensory Scores (Light Touch and Pin Prick) between 180 days and baseline
- Change in ISNCSCI Upper Extremity Motor Score between 180 days and baseline
- Change in ISNCSCI Lower Extremity Motor Score between 180 days and baseline

- Change in Short Form 36 Version 2 (SF-36v2™) PCS, MCS and 8 dimensions between 180 days and pre-injury (recall)
- Change in EQ-5D health utility between 180 days and pre-injury (recall)
- Graded Redefined Assessment of Strength Sensibility and Prehension (GRASSP) at 14 days or Discharge (whichever occurs first) and 180 days
- Change in Numeric Pain Rating Scale (pain NRS) at 14 days, 84 days and 180 days

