### *6.7.7 Study Schematic*

---

The schedule of visits and data to be collected at each visit is shown in Table 1. All visits are preferred to be performed in the clinic. However, if the subject is unable to visit the clinic, a study investigator or an assigned examiner may visit the subject to collect the data. Data collection by phone and/or mail is not permitted.

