\*Data should be entered into the eCRF within 48 hours, but no later than 14 calendar days from collection; \*\*MRI between 48-72 hours at the discretion of the Investigator; & Medication compliance should be completed daily; \*\*\*GRASSP will be performed at 14 days or Discharge (whichever occurs first); § Recall of status prior to the injuryStudy Timeline

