#### *6.7.7.7 Discharge from acute care*

---

The following activities should be performed during the visit:

- Obtain and record concomitant medications
- Obtain and record AE/SAE
- Obtain and record vital signs
- Perform GRASSP if discharged from acute care before 14 days follow-up
- Obtain and record physical and occupational therapy information
- Complete discharge information
- Schedule next study visit
- Check SWs for completeness
- Verify data and enter into eCRF preferably within 48 hours but no later than 14 calendar days from collection

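### The early GRASSP is timed by discharge from acute care when that precedes day 14, so a post-randomization event sets when this Other endpoint is measured

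*Protocol*

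**What the plan says.** Section 6.3.3 lists, among the other endpoints, GRASSP "at 14 days or Discharge (whichever occurs first) and 180 days". The synopsis gives the same definition, and the Table 1 footnote repeats it: "GRASSP will be performed at 14 days or Discharge (whichever occurs first".

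The visit lists put the rule into practice. At the 14-day visit (Section 6.7.7.6) the item reads "GRASSP evaluation (if discharge from acute care has not yet happened". At the discharge visit (Section 6.7.7.7) it reads "Perform GRASSP if discharged from acute care before 14 days follow-up". A subject discharged before day 14 therefore has a GRASSP at discharge and none at day 14.

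Section 6.7.7 governs how visits are held. It states "Data collection by phone and/or mail is not permitted", and provides that "if the subject is unable to visit the clinic, a study investigator or an assigned examiner may visit the subject to collect the data".

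The statistical section differs. Section 7.3 names GRASSP at 84 and 180 days and gives no early time point. Neither Table 1 nor the 84-day visit list (Section 6.7.7.8) schedules a GRASSP at day 84.

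**The concern.** An endpoint meant to compare randomized arms should be measured at a time that treatment cannot move. Discharge from acute care comes after randomization and can plausibly depend on recovery and complications, both of which the drug might affect. If riluzole shortened the acute stay, its subjects would be scored earlier in recovery and the early comparison would be tilted against it. If adverse effects lengthened the stay, the tilt would favour it.

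Analysis cannot fully repair this. The day-14 score is never collected in subjects who leave earlier, and adjusting for the day of examination conditions on a post-randomization variable. Table 1 schedules no baseline GRASSP, so there is no earlier score to serve as an anchor.

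**Working it through.** The plan gives no figure for this point, so there is none to reproduce. The check is a comparison of sections plus two short calculations.

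**1. Is the rule stated consistently?** The synopsis, Section 6.3.3, the Table 1 footnote and Sections 6.7.7.6 and 6.7.7.7 all give discharge or day 14, whichever is first. The rule is deliberate and not a slip in one place. Section 7.3 is the exception.

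**2. Is the discharge condition needed?**
- Day-14 visit (6.7.7.6): ISNCSCI, SCIM, vital signs, laboratory tests and pain NRS carry no discharge condition. GRASSP is the only conditional item.
- Discharge visit (6.7.7.7 and Table 1): neither ISNCSCI nor SCIM is scheduled, so a discharge GRASSP has no such examination beside it.
- Day-180 visit (6.7.7.9): GRASSP is done with no discharge condition, so the protocol already expects it to be performed after acute care.
- Mode of visit (6.7.7): in person, with an examiner travelling to the subject if necessary.

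So every subject due the 14-day visit is already to be examined in person by someone performing ISNCSCI and SCIM. Deaths, withdrawals and missed visits are the exceptions.

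**3. Where does a discharge examination fall in the treatment course?** Under Sections 6.7.2.1 and 6.7.2.2, doses 1 and 2 are at 0 and 12 h. Dose 3 follows dose 2 by 4 to 16 h, and doses 4 to 28 follow at 12 h steps.
- Dose 28 = 12 + (4 to 16) + 25 × 12 = 316 to 328 h, or about day 13.2 to 13.7.
- For illustration, take a discharge at 96 h. Dose 8 falls at 12 + (4 to 16) + 5 × 12 = 76 to 88 h, dose 9 at 88 to 100 h and dose 10 at 100 to 112 h. That GRASSP would follow 8 or 9 of the 28 doses.

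A discharge GRASSP before about day 13 is thus taken during the course, and a day-14 GRASSP is normally taken at or after its end.

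**4. What form does the bias take?** Let *s* be the recovery slope in GRASSP points per day, treated as linear. Let *f* be the difference between arms in the proportion discharged before day 14, and *d* the mean number of days by which those examinations precede day 14, taken as equal in both arms.
- Difference in mean examination day = *f* × *d*.
- Shift in the arm difference from timing alone = *f* × *d* × *s*.
- If discharge times do not differ by arm, *f* = 0 and the mean shift is about 0. Examination day *T* then adds about *s*² × Var(*T*) to the variance of the score, if *T* is unrelated to the subject's level.

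The documents supply none of *s*, *f* or *d*. Purely as assumed ranges, *f* = 0.10 to 0.20 and *d* = 5 to 8 days give 0.10 × 5 = 0.5 to 0.20 × 8 = 1.6 days. With *s* assumed at 0.5 to 2 points per day, the shift would be 0.5 × 0.5 = 0.25 to 1.6 × 2 = 3.2 points. These values show how the formula behaves and are not an estimate for this trial.

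**5. What else depends on it?** The 316 evaluable and 351 enrolled subjects in Section 7.9 rest on the motor score at 180 days. Nothing there uses GRASSP.

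**The case against.** The strongest reply is that little hangs on this. GRASSP is neither primary nor secondary, no alpha or success criterion rests on it, and the 180-day GRASSP is taken whatever the discharge date. That stands, and it limits the weight of the point.

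Second, a reader might infer that the protocol pools discharge and day-14 scores in one analysis. It does not say so. No analysis of the early GRASSP is described, Section 7.3 omits it, and Section 7 leaves details to the SAP. This also stands. What remains is that the two timings are defined as a single listed endpoint, and that the day-14 score is not collected in subjects discharged early. No SAP can supply it.

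Third, a reader might infer that the early comparison is in fact biased. No section says that riluzole alters length of stay or that discharge depends on recovery. Allocation is stratified by site (synopsis) and blocked within center (Section 7.14), so discharge timing driven by site practice should be roughly balanced. The dosing instructions are also written largely around hospital administration, which suggests that very early discharge may be uncommon, although no rate is given. The bias is therefore conditional on a treatment effect on discharge before day 14. Without one, only added variance remains.

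Finally, it may be said that discharged subjects are hard to examine. That does not fit the protocol's own schedule, which requires in-person ISNCSCI and SCIM at day 14 regardless of discharge and GRASSP at day 180.

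**Conclusion.** The point holds as a modest design weakness. A post-randomization event sets when the early GRASSP is measured, and the condition is unnecessary given the in-person examination already scheduled at day 14. If treatment affects time to discharge, the early arm comparison is biased, in a direction that depends on the sign of that effect. If it does not, the cost is extra variance and a mixture of time points.

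The size is unknown because the documents give no discharge times and no GRASSP slope. The stronger readings, that a material bias has been shown or that the trial's main conclusions are exposed, are not supported. The primary and secondary endpoints, power, sample size and 180-day GRASSP are unaffected.

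The disagreement between Section 7.3 and the other sections is a plain inconsistency. It leaves open whether the early GRASSP is an analysed endpoint at all.

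**What to change.** Require GRASSP at the 14-day visit, in the same window as ISNCSCI and SCIM, in all subjects due that visit, whether or not they have been discharged. Carry the change through every place that states the rule:
- the synopsis and Section 6.3.3: replace the discharge-or-day-14 definition with day 14;
- Table 1 and its footnote: remove the GRASSP entry under discharge and the footnote condition;
- Section 6.7.7.6: remove the condition on discharge;
- Section 6.7.7.7: remove the GRASSP instruction;
- Section 7.3: reconcile its 84- and 180-day time points with Section 6.3.3 and the schedule, and state whether the early GRASSP is analysed.

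The cost is protocol wording and no new visit. For subjects discharged early, the examination moves to a visit already scheduled. The downside is that some of them will miss the 14-day visit and have no early GRASSP. If a discharge GRASSP is kept to cover this, it has to be done before anyone knows whether day 14 will be missed, so it means a second examination in subjects discharged early. It should then be an additional dated record and should not stand in for the day-14 value.

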#### *6.7.7.7 Discharge from acute care*

---

The following activities should be performed during the visit:

- Obtain and record concomitant medications
- Obtain and record AE/SAE
- Obtain and record vital signs
- Perform GRASSP if discharged from acute care before 14 days follow-up
- Obtain and record physical and occupational therapy information
- Complete discharge information
- Schedule next study visit
- Check SWs for completeness
- Verify data and enter into eCRF preferably within 48 hours but no later than 14 calendar days from collection

#### *6.7.7.8 84 days $\pm$ 14 days*

---

The following activities should be performed during the visit:

- Obtain and record concomitant medications
- Obtain and record AE/SAE
- Obtain and record physical and occupational therapy information
- Investigator performs and records:
  - ISNCSCI
  - SCIM
- Subject completes questionnaires for:
  - EQ-5D
  - SF-36v2™
  - Pain NRS
- Schedule next study visit
- Check SWs for completeness

- Verify data and enter into eCRF preferably within 48 hours but no later than 14 calendar days from collection

#### *6.7.7.9 180 days $\pm$ 30 days*

---

This is the main endpoint study visit. The following activities should be performed during the visit:

- Obtain and record concomitant medications
- Obtain and record AE/SAE
- Obtain and record physical and occupational therapy information
- Investigator performs and records:
  - ISNCSCI
  - SCIM
  - GRASSP evaluation
- Subject completes questionnaires for:
  - EQ-5D
  - SF-36v2™
  - Pain NRS
- Schedule next study visit (if applicable)
- Check SWs for completeness
- Verify data and enter into eCRF preferably within 48 hours but no later than 14 calendar days from collection

#### *6.7.7.10 365 days $\pm$ 45 days*

---

The following activities should be performed during the visit:

- Obtain and record concomitant medications
- Obtain and record AE/SAE
- Obtain and record physical and occupational therapy information
- Investigator performs and records:
  - ISNCSCI
  - SCIM
- Subject completes questionnaires for:
  - EQ-5D
  - SF-36v2™
  - Pain NRS
- Check SWs for completeness
- Verify data and enter into eCRF preferably within 48 hours but no later than 14 calendar days from collection

#### *6.7.7.11 Unscheduled Visit*

---

- Obtain and record concomitant medications
- Obtain and record AE/SAE
- Check SWs for completeness

- Verify data and enter into eCRF preferably within 48 hours but no later than 14 calendar days from collection

#### *6.7.7.12 Dispensing the Investigational Drug*

---

Each study site will be supplied with the Investigational Drug. All Investigational Drug containers will have an identical appearance. Each container will be labeled with a unique number that will match a number in a randomization envelope.

Authorized site research staff will select the Investigational Drug package to dispense to the subject by matching the container label to the unique randomization number identified in the randomization envelope.

- Authorized Hospital Staff/Nurse will be instructed as follows:
  - Subject to be given one capsule every 12 hours via oral or NG administration (see additional explanations at Section 6.7.2)
  - The investigational drug should be taken at least an hour before, or two hours after a meal to avoid a food-related decrease in bioavailability. If a dose is missed, the next dose should be administered as originally planned

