#### *5.2.8.1 Preparation of Investigational Drug*

---

Active. The riluzole tablets will be pulverized into powder. Based on the packing statistics of the pulverized powder and desired strength of the capsules needed, microcrystalline cellulose will be added to completely fill the capsules. Capsules will be gelatin-based and BSE- and prion-free certified. This method of preparation is preferred to over-encapsulation of the riluzole tablets in this particular study to allow the contents of the capsule to be administered to participants that are on a nasogastric feeding tube.

Placebo. Same as the active capsules but will only contain microcrystalline cellulose.

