### 6.2 Study Objectives

---

The aim of this study is to evaluate efficacy and safety of riluzole in the treatment of patients with acute SCI. The primary objective is to evaluate the superiority of riluzole, at a dose of 100 mg BID for the first 24 hours followed by 50 mg BID for the following 13 days after injury, as compared to placebo, in change between 180 days and baseline in motor outcomes as measured by International Standards for Neurological Classification of Spinal Cord Injury Examination (ISNCSCI) Motor Score, in patients with acute traumatic SCI, presenting to the hospital less than 12 hours after injury. Secondary objectives are to evaluate the effects of riluzole on overall neurologic recovery, sensory recovery, functional outcomes, quality of life outcomes, health utilities, mortality, and adverse events. The working hypothesis is that the riluzole treated subjects will experience superior motor, sensory, functional, and quality of life outcomes as compared to those receiving placebo, with an acceptable safety profile.

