## 6.7.2 Investigational Drug Dose and Administration

### 6.7.2.1 Dose

Subjects will receive a total of 28 doses of Investigational Drug, administered twice a day, for a total of 14 days. The riluzole group will receive riluzole in a dose of 100 mg at 0 hours and 12 hours (doses 1 and 2) followed by 50 mg doses every 12 hours for the next 13 days (doses 3 - 28). The control group will receive placebo capsules in a dose of two capsules at 0 hours and 12 hours (doses 1 and 2) followed by one capsule every 12 hours for the next 13 days (doses 3 to 28).

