#### *6.7.7.16 Assessment of Subject Compliance*

---

Compliance will be recorded by the Study Research Coordinator or Investigator during enrollment at 14-day post-enrollment and will be documented on the appropriate SW (Medication Compliance SW). Subjects must have 80% or greater compliance. The subject is considered compliant if he/she has taken at least 24 capsules.

Failure to comply will be considered a Protocol Violation and will be recorded on the Protocol Violation Form. Non-compliant subjects will remain in the study and will undergo the same study procedures as compliant subjects.

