### *7.13.4 Per-protocol Population*

---

The Per-protocol population (PP) population is a subset of CC population and it includes all enrolled patients entirely consistent with the Protocol and who received at least 80% of study-directed treatment and had 180 days of follow-up. Any visits where Protocol violations occurred will be reviewed for possible exclusion from PP population.

The patients with major Protocol violations will be tabulated by violation type and affected visit(s), where applicable. All Protocol violations will be listed.

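### The staff instruction in Section 6.7.7.12 gives one capsule at every dose, but Section 6.7.2.1 requires two at doses 1 and 2

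*Protocol*

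**What the plan says.** Section 6.7.7.12, on dispensing, sets out how authorized hospital staff or nurses are to be instructed. Its first item reads: "Subject to be given one capsule every 12 hours via oral or NG administration (see additional explanations at Section 6.7.2". It makes no exception for any dose.

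Section 6.7.2.1 sets 28 doses over 14 days. For the active arm: "The riluzole group will receive riluzole in a dose of 100 mg at 0 hours and 12 hours (doses 1 and 2", then 50 mg for doses 3 to 28. For the control arm: "placebo capsules in a dose of two capsules at 0 hours and 12 hours (doses 1 and 2", then one capsule for doses 3 to 28.

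Section 5.2.8.1 describes the placebo: "Same as the active capsules but will only contain microcrystalline cellulose". Section 6.7.4 blinds subjects, investigators and research personnel to allocation.

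The primary objective in Section 6.2 names the regimen under test: "at a dose of 100 mg BID for the first 24 hours followed by 50 mg BID for the following 13 days after injury". The synopsis and Section 6.1 give the same regimen.

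Section 6.7.7.16 requires at least 80% compliance and puts it in capsules: "The subject is considered compliant if he/she has taken at least 24 capsules". Section 7.13.4 limits the per-protocol population to subjects "entirely consistent with the Protocol and who received at least 80% of study-directed treatment and had 180 days of follow-up".

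**The concern.** The bullet states the maintenance count as if it covered the whole course. It is right for doses 3 to 28 and wrong for doses 1 and 2, which are the loading doses. It is also the text meant for the people who hand over the capsules. They work with containers of identical appearance, and the label items listed in Section 5.2.8.2 include no dosing direction, although country rules may add one.

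At stake is whether the active arm receives the regimen named in the primary objective. If the bullet alone governed both loading doses, the active arm would receive 50 mg at each of 28 doses. That is the Phase I regimen described in Section 5.2.6, not the one this trial sets out to test. Such a shortfall would also pass the protocol's two numeric compliance checks.

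**Working it through.** **Inputs**

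- Number of doses: 28 (Section 6.7.2.1).
- Riluzole: 100 mg at doses 1 and 2, 50 mg at doses 3 to 28 (Section 6.7.2.1).
- Placebo: two capsules at doses 1 and 2, one capsule at doses 3 to 28 (Section 6.7.2.1).
- Staff instruction: one capsule at each dose (Section 6.7.7.12).
- Compliance threshold: 80%, equated with 24 capsules (Section 6.7.7.16).
- Capsule strength: not stated. I assume 50 mg, which the 100 mg and 50 mg doses and the matched capsules imply. Only the milligram figures below need this.

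**Step 1: which capsule count reproduces the plan's own threshold?**

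- Section 6.7.2.1: 2 × 2 + 26 × 1 = 30 capsules, and 0.80 × 30 = 24. This is the stated threshold exactly.
- Section 6.7.7.12 read literally: 28 × 1 = 28 capsules, and 0.80 × 28 = 22.4, so 23 capsules would be needed. The stated 24 would be 24/28 = 85.7%.

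The compliance rule was therefore written for two capsules at doses 1 and 2. Section 6.7.2.1 gives that count in words only for placebo. For riluzole it follows from the matched capsules, the blinding and this arithmetic. The contradiction stands on the placebo count alone.

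**Step 2: what would be delivered if the bullet were followed without its cross-reference?**

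Dose 1 is given at the screening/enrollment visit, where Section 6.7.7.2 has staff administer the first dose "of Investigational Drug and record on the Investigational Drug Dispensing SW". It may therefore be given correctly even if dose 2, due 12 hours later, is not. Both cases are shown.

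| Case | Capsules, whole course | Riluzole over doses 1 and 2 | Riluzole, whole course |
|---|---|---|---|
| Section 6.7.2.1 | 30 | 2 × 100 = 200 mg | 200 + 26 × 50 = 1500 mg |
| Bullet governs dose 2 only | 2 + 1 + 26 = 29 | 100 + 50 = 150 mg (150/200 = 75%) | 150 + 1300 = 1450 mg (1450/1500 = 96.7%) |
| Bullet governs doses 1 and 2 | 28 | 2 × 50 = 100 mg (100/200 = 50%) | 100 + 1300 = 1400 mg (1400/1500 = 93.3%) |

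**Step 3: would the numeric checks catch it?**

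- 24-capsule rule: 29 − 24 = 5 and 28 − 24 = 4 capsules above the threshold. Both cases pass.
- 80% part of the per-protocol definition: 96.7% and 93.3%. Both cases pass.

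**The case against.** The strongest reply is that the sentence carries its own remedy. It sends the reader to Section 6.7.2, the protocol's authority on dosing, which lists the doses by number. Section 6.7.2.2 adds that the first two doses must follow the protocol schedule. The loading dose is stated consistently in the synopsis and in Sections 6.1 and 6.2, and the bullet is right for 26 of 28 doses. On this reading it is an incomplete shorthand.

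The route to harm is also narrow. Dose 1 falls within the enrollment visit, and Section 6.7.7.14 has the drug dispensed under the investigator's direction and in line with the protocol. Other controls could expose an error:

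- medication compliance is completed daily (Table 1 footnote);
- amounts dispensed to each subject are logged (Section 6.7.7.15);
- per-protocol status requires full consistency with the protocol as well as 80% of treatment (Section 7.13.4);
- the first periodic monitoring visit is expected after the first one or two subjects at a site (Section 12.5.3).

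Any 80% rule tolerates two missed capsules by design, so passing it proves little. The site instruction sheet and the worksheets are not part of the document, so whether they repeat the wording, or record capsules per dose, cannot be seen.

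All of this stands, and it limits the practical risk. It does not make the stated count correct. The bullet gives a definite number, signals no exception, and labels the reference as further explanation. A reader could take that to mean the timing, tube and feeding details in Section 6.7.2.2. An explanation should not have to overrule the instruction it explains.

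**Conclusion.** The inconsistency is real: the capsule count in Section 6.7.7.12 is wrong for doses 1 and 2. The intended count is two capsules at each, as Section 6.7.2.1 and the 24-capsule threshold show.

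The effect on delivered drug is conditional. If staff follow the cross-reference, there is no shortfall. If they act on the bullet alone, and capsules hold 50 mg, the active arm receives 75% of the intended drug over doses 1 and 2 (dose 2 affected) or 50% (both affected), and 96.7% or 93.3% over the whole course. No under-dosing has been shown to occur. The finding has no bearing on sample size, alpha or power. It merits correction because it is an operative dosing instruction for the regimen named in the primary objective, and because the numeric compliance checks would not reveal the error.

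**What to change.** Reword the bullet in Section 6.7.7.12 to say: two capsules at doses 1 and 2 (0 and 12 hours), then one capsule at each of doses 3 to 28, timed as in Section 6.7.2.2. Carry the same wording into the site instruction sheet. Leave Section 6.7.2.1 and the 24-capsule threshold as they are, since they already agree.

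The cost is one sentence in the protocol and the matching line in the site material. The regimen, the compliance rule and the analyses do not change.
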